### Patient and public involvement

Several steps were undertaken to secure active involvement of participants. First, we referred in all personal interactions with participants as well as all written study documents to participants as study partners to promote an open and mutual appreciation communication style. Second, the apps were developed and refined based on findings from prior pilot studies conducted with similar target groups. Third, a feedback app specifically designed by SMART-AGE software engineers was used during the full trial to collect detailed feedback from study partners using the apps. Finally, post-study events are planned to share results and gather input for future research.

In terms of dissemination, SMART-AGE not only aims for scientific publishing at the highest quality levels possible but also strives to translate its findings to the community ecology which serve as study platforms and hopefully later beyond. To make this come true, SMART-AGE invests in continuous contact and information exchange with community authorities, local senior organizations, and the general medical community. More specifically, SMART-AGE will do two intensive feedback meetings separated by community. Also, a public event for presenting the main findings is envisaged in cooperation with city authorities involved. We also have definite plans for a senior citizen workshop to further discuss the ethically oriented findings of SMART-AGE. SMART-AGE also is in contact with Heidelberg University’s Innovation Hub to prepare a possible dissemination of further improved apps in a later set.

### Outcomes

There are four primary outcome domains in this study that will be compared across all three study arms:Health-related self-awareness, control beliefs, and self-efficacy, which includes measures like the Health Locus of Control Scale [48], Health Literacy [49], Adapted Health Consciousness Scale [50], and Self-efficacy [51];Motor capacity and performance, which includes measures like the Timed Up and Go Test [52] and movement sensor-based physical activity parameters (e.g., steps per day) using Axivity AX6 sensors;Loneliness and social support, which includes measures like the UCLA Loneliness Scale [53], Lubben Social Network Scale [54].Technology acceptance, competence, and usage, which includes measures like Computer Anxiety [55] and End User Frustration [56].

Another important part of the assessment architecture in SMART-AGE is the generation of multiple usage data while the apps are used by study partners. This includes, for instance, the assessment of weekly usage frequency and intensity (e.g., total time spent using the apps, number of interactions within the apps), as well as the analysis of app-specific features used—such as whether video calling was utilized in smartVERNETZT, how many training levels were completed in KOKU, or how many questions were answered in smartIMPULS or smartFEEDBACK. These metrics will be analyzed over time and across multiple apps to identify usage patterns and dynamics, which can then be related to changes in the targeted outcomes.

A complete list of all assessments, encompassing all measures related to the main and secondary hypotheses, as well as demographic measures that describe the sample is provided in Appendix Part 2. In addition, we also collect objective user data from the SMART-AGE apps to evaluate in more detail the app usage.

### Sample size

The sample size was determined through an a-priori power analysis to ensure adequate power for the planned structural equation modeling analyses. We will study the effect of the intervention groups as contrasted with the active control condition on main outcomes using latent change models, in which each of the four main outcome domains will be represented in latent space by at least three manifest variables. Assuming measurement invariance across the three study time points, the two intervention sites, and the two experimental groups and one active control group, this results in a model with 128 estimated parameters and 16,162 degrees of freedom. With the requirement of five participants per estimated parameter, an expected dropout rate of 10% and a further increase to balance the strata, we plan to collect a sample of 720 participants to be analyzed based on an intention-to-treat analysis, that is, all participants having entered the study at baseline will become part of the statistical effect analysis independent of their “fate” along the full observational period. Moreover, at each of the three study time points for each of the three groups, the planned sample size meets Browne and Cudeck’s [57] recommendations for model testing based on the close fit hypothesis (H0, ε ≤ 0.05; H1, ε ≥ 0.08; *α* = 0.05) using the root mean square error of approximation (RMSEA; 44). This provides a statistical power of 1 – *β* > 0.99 for the main model across all study time points as well as for analyses conducted at a single time point, ensuring that the study has sufficient power to reject the model if its fit to the empirical data is inadequate.

To ensure a certain level of diversity, a two-fold recruitment strategy was applied. First, participant recruitment was based on random sampling of addresses provided by local city registries. Due to German data protection regulations, researchers were only allowed to send out initial invitation letters without follow-up reminders. To lower the participation threshold, the invitation package included a letter of support from the city mayors, framed the study as a unique learning opportunity, and offered the intervention tablet as an incentive. Second, sampling was conducted in two socioeconomically contrasting cities: one, a historically preserved university city; the other, a traditionally working-class city with significant World War II destruction and one of the highest proportions of migrant populations in Germany.

We will include as many participants as possible until the end of August 2024. If we do not manage to obtain our sampling goal of 720 participants, we will, following what has been said in the study’s preregistration, consult the advisory board and recruit as many participants as needed to reach the next multiple of 72 to balance the eight strata.

### Blinding

Participants are always aware of the study arm they are assigned to, as they either have access to none, two, or all four of the project apps, except during the baseline assessment. To gather data, two HVs, HV I and HV V, are conducted. It is crucial that the researchers conducting these visits remain blinded to the participants’ group assignments. To facilitate this, the research team is divided into two distinct groups: assessors and app-instructors. The assessors are responsible for data collection during HV I and HV V, while the app-instructors handle HV I, II, III, and IV. The initial HV occurs prior to the randomization of participants, allowing both assessors and instructors to be involved in this stage of the study. We do not anticipate any requirement for unblinding the assessors, but if required, the project coordinators will have access to group allocations and any unblinding will be reported. The randomization list used to allocate participants to the study arms was created by the lead study statistician and the project coordination team, who are the only ones with access to the data file containing personalized information. After individuals are screened positive, the project coordination allocates them to the randomly selected study arm using a study management software. The software allows the information of the allocated study arms to be hidden from blinded assessors while showing it to user groups who need this information.

## Methods: data collection, management, and analysis

### Data collection methods

At each of these two time points (T1 and T6), trained researchers will visit participants at home and conduct a number of assessments (see Appendix–A2), including a battery of cognitive tasks and the application of state-of-the-art body-fixed movement sensors (Axivity AX6, Axivity Ltd, Newcastle upon Tyne) to measure physical activity for 7 consecutive days. Moreover, participants will be asked to complete a set of web-based questionnaires using their tablet within a week of each of these visits by means of a RedCap data architecture. Web-based questionnaires are sorted into four sets of comparable length that each take no longer than an hour to complete. Participants will be asked to respond to one set of questionnaires per day. After the second and fourth set of questions, participants perform further cognitive tasks on the tablet. The first set of questions, presented on the first day, includes the primary outcome measures and is repeated at T3 in order to have a higher granularity of primary outcome data.

### Data management

Data storage and data processing are subject to the highest standards of data security. First, no personally identifiable data is processed outside the EU. Second, all questionnaire-based online assessments are conducted using a REDCap instance hosted on a secure cloud at Heidelberg University, ensuring strict compliance with data security requirements. The SMART-AGE apps are also located in the same secure cloud system. Third, the REDCap data and the app data are exclusively transmitted in encrypted form from the tablets to the respective cloud server. Subsequently, the data is securely transferred to a high-security research data server, also located within the University of Heidelberg. This server is the central location to which all data from the main project (including the data from the sensors, the apps, and the cognitive assessments) and, if possible, the data from the sub-studies are transferred.

All analyses with pseudonymized data must be performed directly on the server. Each researcher can only access the specific data they are directly responsible for, for the purpose of monitoring data quality or to which they have been granted access by the principal investigators. This personalized access is provided after an internal multi-stage review process of the submitted statistical analysis plan.

Constant supervision and analysis of the multilevel data infrastructure is an essential part of the lead statistician’s work package. To achieve high data quality and immediate data access, online questionnaires orchestrated by the software REDCap are used to a large extent to minimize data entry errors. Closed question formats are mainly used and when an open format for quantification is necessary, plausible value ranges are specified in advance to detect invalid values. A data preprocessing script undergoing continuous updating was generated in advance in the programming language R to correct defined mistakes in the data, such as misspelled IDs or duplicate entries created due to internet connection problems.

The de-identified data set of the SMART-AGE study will be shared in a secure data repository of Heidelberg University after the completion of the study.

### Statistical methods

Our main hypotheses will be tested using multilevel and structural equation models, following an intention-to-treat analysis. We will test the effect of experimental group on primary outcomes separately for each outcome with a 3 × 3 factorial design multilevel model with the between-subjects factor *study arm* (active CG vs. partial IG vs. full IG) and the within-subjects factors *study time point* (study start vs. 3 months vs. 6 months), followed by post-hoc comparisons controlling for the family-wise error rate. Models will include random intercepts for each participant and their place of residence. As covariates, we will consider participants’ gender, their age, and their frequency and intensity of app usage. We plan to report all analyses with and without the inclusion of these covariates. Where the assessment of primary outcomes is only possible during HVs, we will remove the 3-months level from the within-subjects factor *study time point*.

In addition, we will test the effect of experimental groups on primary outcomes first separately for each outcome and then jointly for all four primary outcomes using latent change models. In these models, the multilevel structure of the data will be accounted for by multigroup comparisons to examine whether (a) the effects of the two IGs are larger than the effects of the active CG (see hypotheses), whether (b) the effects of the full IG are larger than the effects of the partial IG (see hypotheses), and (c) by which individual and/or sociodemographic variables the effects of the two interventions on the four primary outcome variables are moderated.

For all statistical tests, we will use alpha = 0.05 as the threshold for statistical significance. Post-hoc comparisons will be controlled for the family-wise error rate. We will be reporting standardized effect sizes and confidence intervals whenever possible. In addition, we will evaluate the goodness-of-fit of SEMs based on the comparative fit index [CFI; [59]] and the root mean square error of approximation [RMSEA; [39]] and compare model fits with the Akaike Information Criterion [AIC; [60]] and the likelihood ratio test. Following the recommendations by Browne and Cudeck [58] and Hu and Bentler [61], we consider CFI values > 0.90 and RMSEA values < 0.08 to indicate acceptable model fit and CFI values > 0.95 and RMSEA values < 0.06 to indicate good model fit. AIC differences ≥ 10 will be interpreted to indicate a substantial advantage in relative model fit in direct model comparisons [62]. We will assess the statistical significance of model parameters with the two-sided critical ratio test. To our knowledge, this is the first study to systematically monitor and evaluate long-term app usage in a German sample of older adults. We therefore lack the necessary prior knowledge to determine exclusion criteria for app usage and engagement with the tablet. Thus, a blinded analyst [63] will screen study partners’ app usage after the data is collected to propose appropriate criteria. The blinded analyst will not have access to the outcome variables, protecting the confirmatory nature of the statistical inference.

Outlier values in measured variables (assessments) will be removed if they exceed ± 3 SD of the sample mean of their respective study arm and study time point. In addition, we will exclude individuals whose responses appear random (e.g., identical responses to all questions). Physical activity data will only be included if the individual has worn the sensor for at least 4 days.

The type of missing data will be assessed and accounted for using the full information maximum likelihood method in all statistical models. If data are found to be Not Missing at Random, this will be addressed appropriately to minimize potential bias and stated as a limitation.

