Hypotheses based on these treatment variations are as follows:Participants who use a tablet equipped with the smartVERNETZT app (full and partial IG), which encourages social networking and participation, are expected to experience lower levels of loneliness and higher levels of social engagement compared to those using a tablet with only standard applications. This effect is expected to be even larger in the full IG than in the partial IG due to the synergistic benefits derived from using all apps designed to enhance quality of life.Participants who are in the full IG (who all have access to smartIMPULS) have increased health-related self-awareness and health-related control beliefs, compared to the active control and the partial IG, who both do not have access to smartIMPULS. Between the latter two groups, we do not expect any differences in health-related self-awareness and health-related control beliefs.Participants who are in the full IG (who all have access to KOKU) will show better gait performance and motor functioning, compared to the active control and the partial IG, who both do not have access to KOKU. Between the latter two groups, we do not expect any differences in gait performance and motor functioning.Over time, participants using a tablet will report greater technology acceptance and develop technology-related skills than before using a tablet. This increase in technology acceptance and technology-related skills is larger for participants in the full and partial IG. In addition, exploratory analysis will give more insight into the dose–response relationship between the amount of apps and their impact on technology acceptance and technology-related skills***.***

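### Comparisons hypothesised in advance (H1–H3) are handled as corrected post-hoc tests in the multilevel model; planned contrasts would match the hypotheses and, under common corrections, keep more power

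*Protocol article*

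**What the plan says.** **Hypotheses (Objectives).** For H1, users in the full and partial IG "are expected to experience lower levels of loneliness and higher levels of social engagement compared to those using a tablet with only standard applications". The text adds: "This effect is expected to be even larger in the full IG than in the partial IG". For H3, the full IG "will show better gait performance and motor functioning, compared to the active control and the partial IG". H2 has the same form for health awareness and control beliefs. Both H2 and H3 state that no difference is expected between partial IG and control.

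**Multilevel analysis (Statistical methods).** Group effects are tested "separately for each outcome with a 3 × 3 factorial design multilevel model with the between-subjects factor" of study arm and a within-subject factor of time (start, 3 months, 6 months), "followed by post-hoc comparisons controlling for the family-wise error rate". The 3-month level is dropped for outcomes that can only be measured at home visits. The section later repeats: "Post-hoc comparisons will be controlled for the family-wise error rate". On thresholds it says: "For all statistical tests, we will use alpha = 0.05 as the threshold for statistical significance" and "We will assess the statistical significance of model parameters with the two-sided critical ratio test".

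**Latent change models (same section).** These are added to the multilevel analysis and name two contrasts for all four outcome domains, each with a pointer to the hypotheses: (a) the two IGs against control and (b) full against partial. The text does not say whether the multilevel or the latent change result decides.

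**The concern.** A comparison that the hypotheses name in advance is a planned comparison. Treating it as post hoc has two consequences.

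First, the 3 × 3 model yields an arm main effect, an arm-by-time term and several pairwise tests, and these can disagree for the same outcome. The plan does not say which of them answers H1, H2 or H3.

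Second, a family-wise correction over the arm pairs can cost power without buying protection that H2 and H3 need. If such a claim requires full to beat both control and partial, testing each at 0.05 already holds the rate of false claims at or below 0.05.

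The sample size section offers no margin to absorb a loss, because it rests on parameter count and model fit and not on any difference between arms.

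**Working it through.** **The plan's own figure.** 128 parameters × 5 = 640; 640 / 0.90 = 711.1, so 712; the next multiple of 72 is 720, or 240 per arm. The stated 720 reproduces. The stated power above 0.99 for the RMSEA test also reproduces (about 1.00 with 16,162 degrees of freedom at N = 240 or 720). Neither figure concerns an arm contrast.

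**Which term decides.** The time factor includes the pre-randomisation baseline, where the expected arm difference is zero. The arm main effect averages over time points:
- Two time points (home-visit outcomes): (0 + d)/2 = 1/2 of the T6 effect.
- Three time points: (0 + T3 effect + d)/3, which is 1/3 of the T6 effect if nothing has happened by T3 and 2/3 if the T3 effect equals the T6 effect. For H2 the lower end is relevant, since smartIMPULS is introduced only after the T3 assessment.

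The change from T1 to T6 does not have this dilution.

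**Power for H2/H3.** Inputs: n = 240 × 0.90 = 216 per arm (10% dropout, Sample size section); unit SD; full IG shifted by d, the other two arms equal; two-sided 0.05. The article gives no target effect. d = 0.17 and 0.28 are the earlier PRISM trial's values quoted in its background section, and 0.25 is illustrative.

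One pair: expected z = d × √(n/2). At d = 0.25 this is 0.25 × √108 = 2.598.
- Unadjusted: Φ(2.598 − 1.960) = Φ(0.638) = 74%.
- Bonferroni over three pairs (critical value 2.394): Φ(0.204) = 58%.

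Both pairs: full vs control and full vs partial share the full arm (correlation 0.5), so joint power was simulated.

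| Rule for the two contrasts | d = 0.17 | d = 0.25 | d = 0.28 |
|---|---|---|---|
| Both required, each at 0.05 | 26% | 60% | 73% |
| Omnibus gate, then unadjusted pairs | 25% | 60% | 72% |
| Holm, three pairs | 17% | 48% | 62% |
| Tukey, three pairs | 14% | 44% | 58% |
| Bonferroni, three pairs | 13% | 42% | 55% |

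Before rounding, the gate costs 60.3% − 59.6% = 0.7 points at d = 0.25 and 72.6% − 72.1% = 0.5 points at d = 0.28. Using t in place of normal critical values moves entries by about one point at most.

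**Latent change contrast (a) under H2/H3.** If (a) pools the two IGs, the expected difference is d/2 with standard error √(1.5/n). At d = 0.28: z = 0.14 / √(1.5/216) = 0.14 / 0.0833 = 1.68, and power is Φ(1.68 − 1.96) = 39%. Full vs control alone has z = 0.28 × √108 = 2.910 and power Φ(0.950) = 83%. Pooling averages the full IG with an arm that H2 and H3 expect to equal control.

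**The case against.** Four points on the other side carry weight.

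1. **No correction method is named.** An omnibus gate followed by unadjusted pairs is a closed test for three arms at one time point, so it controls the family-wise error rate and fits the wording. It costs less than one point. A reader might infer that the plan as written must lose power; the text does not support that. The loss arises under Bonferroni, Tukey or Holm.

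2. **Contrasts are named elsewhere.** A reader might infer that the plan names no decisive comparison anywhere. The latent change models name two, with reference to the hypotheses. The gap is in the multilevel model, and in contrast (a) for H2 and H3 if it pools the IGs.

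3. **The family need not be large.** A reader might count all 36 pairs of the nine arm-by-time cells and obtain far lower power. That does not fit home-visit outcomes, which have 3 × 2 = 6 cells and 15 pairs, and a family mixing different arms at different times is an implausible reading in any case. Nor can one say that a three-pair correction spends alpha on a pair no hypothesis mentions: H2 and H3 both address partial vs control.

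4. **Some detail belongs in the analysis plan.** The correction method and the exact family can be left to it. The article, however, states both the hypotheses and the test, and they do not match; that mismatch is not omitted detail.

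Requiring both pairs is also one reading of H2 and H3. A single contrast of full against the mean of the other two would be another. Either is a planned contrast, and the multilevel section names neither.

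**Conclusion.** The point holds in a limited form. In the multilevel analysis, comparisons that H1 to H3 state in advance are handled as family-wise-corrected post-hoc tests, and no term, time point or contrast is tied to a hypothesis. The latent change contrasts fit H1, but (a) does not fit H2 and H3 if it pools the IGs.

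The illustrative cost for H2/H3 is 12 to 18 points at d = 0.25 (60% to 48–42%) and 11 to 18 points at d = 0.28 (73% to 62–55%) under common three-pair corrections, and below one point under an omnibus gate. These figures assume 216 per arm, unit SD on the scale analysed, an effect in the full IG only, and effect sizes that the article does not set as targets. The mismatch itself depends on none of these assumptions. It should be corrected.

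**What to change.** For the hypothesised comparisons, replace the post-hoc step in the multilevel model by planned contrasts on the arm-by-time term, as change from T1 to T6:

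- **H2 and H3:** full vs control and full vs partial, both required at two-sided 0.05, with no further correction across these two.
- **H1:** both IGs vs control, then full vs partial, in fixed sequence at two-sided 0.05.
- **Latent change models:** use the same contrasts, so that H2 and H3 are not tested by pooling the partial with the full IG.
- **All other pairs, and all T3 comparisons:** keep the family-wise-corrected post-hoc tests and label them secondary.

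The cost is wording: the same fitted models supply the contrasts, and no extra data are needed. There are two downsides. One significant pair alone no longer supports H2 or H3, and comparisons outside the hypotheses become secondary. The change settles which contrasts decide within an outcome; it does not deal with multiplicity across several outcomes.
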